#### Relevant concomitant care permitted or prohibited during the trial {11d}

Patients in both groups are treated according to the currently established standard of care at the trial center. Any concomitant care as part of routine clinical practice is permitted.

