### Outcomes {12}

#### Primary Outcomes

The primary outcome is the treatment arm failure which is defined as a composite of incomplete hematoma resolution or surgical rescue within 6 months follow-up. Time zero is defined as the date of randomization for both groups in order to ensure comparability and avoid immortal time bias. For patients randomized to the intervention arm, any surgical rescue occurring after randomization but before the scheduled embolization procedure will be considered a treatment failure, and will be included in the intention-to-treat analysis.

Incomplete hematoma resolution is defined as a reduction of the cSDH thickness ≤50% at follow-up compared to the hematoma thickness measured at the time of randomization.

Surgical rescue is intended as hematoma removal for relief or symptoms that developed with continuous growth of the cSDH.

Symptoms onset were evaluated from clinical investigators at follow-up based on Modified Rankin Scale Score (mRS) [20] and Markwalder scale [7]. In particular, patients with mRS≥3 and Markwalder scale≥2 are candidates to surgical evacuation of cSDH.

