#### Secondary outcomes

The following secondary outcomes will be assessed:

Successful embolization rate of the target vessels based on DSA.Complete resolution of cSDH at 6 months follow-up;Recurrence rate of cSDH at 12 months follow-up;Procedure related complication during or 30 day after MMA embolization;Adverse event related to conservative management 30 day after randomization.

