### Assignment of interventions: blinding

#### Who will be blinded {17a}

Due to open-label trial design, the treatment allocation is known to both the treating physician and the patient. In each center is nominated a blinded expert physician that will procure the information concerning clinical outcome at 3, 6 and 12 months. Radiological assessment is also performed by blinded and trained neuroradiologist evaluating non contrast CT scan (NCCT) after 3, 6 and 12 months from randomization. To report to the data safety monitoring board (DSMB), outcome data will be combined with data on treatment allocation by an independent trial statistician. Members of the steering committee are kept blinded of results of interim analyses of efficacy and safety.

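### The surgical-rescue definition lets an evacuation for any other reason score as a treatment success, and the imaging component names no CT visit

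*Protocol article*

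**What the plan says.** Under Primary Outcomes {12}, the protocol article makes treatment failure a "composite of incomplete hematoma resolution or surgical rescue within 6 months follow-up". It defines the two components as follows.

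- Imaging: "Incomplete hematoma resolution is defined as a reduction of the cSDH thickness ≤50% at follow-up compared to the hematoma thickness measured at the time of". The baseline is thus the scan at entry into the trial, and no follow-up visit is named.
- Surgery: "Surgical rescue is intended as hematoma removal for relief or symptoms that developed with continuous growth of the cSDH". This is an indication, with no threshold on any scale.

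The same section then says that symptoms are judged by clinical investigators on the mRS and Markwalder scales, and that "patients with mRS≥3 and Markwalder scale≥2 are candidates to surgical evacuation of cSDH". This sentence gives thresholds and does not mention growth.

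Three other places bear on the point.

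- Relevant concomitant care {11d}: "Any concomitant care as part of routine clinical practice is permitted".
- Who will be blinded {17a}: physician and patient know the allocation, and "Radiological assessment is also performed by blinded and trained neuroradiologist evaluating non contrast CT scan (NCCT) after 3, 6 and 12 months".
- Secondary outcomes: one of these does name its visit, "Complete resolution of cSDH at 6 months follow-up".

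The abstract repeats the two component definitions and adds that, in bilateral disease, one hematoma meeting the criteria is enough for failure.

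**The concern.** A composite failure endpoint should not let the failure event erase its own trace. Here the surgical component counts only when the recorded reason fits the definition. When it does not fit, the patient passes to the imaging component, which is then read on a hematoma that has been surgically removed.

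Whether an operation counts thus depends on a reason recorded by people who know the arm. Blinded assessment at 3, 6 and 12 months cannot undo an open-label decision to operate, and a blinded CT reader would correctly report a thin residual collection. In a trial that expects few failures, a handful of such patients can change the comparison.

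The unnamed CT visit is a smaller problem in the same definition. Two of the scheduled CTs lie within the 6-month window, and the text does not say whether the first can decide the outcome.

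**Working it through.** **1. Apply the definition to patients**

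| Course within 6 months | Rescue as worded? | Reduction of 50% or less? | Score |
|---|---|---|---|
| Evacuated for symptoms with continuous growth | Yes | Irrelevant | Failure |
| Evacuated for growth without symptoms; thin at 6 months | No | No | Success |
| Evacuated under the mRS/Markwalder sentence, continuous growth not documented; thin at 6 months | No | No | Success |
| Evacuated by patient or physician preference; thin at 6 months | No | No | Success |
| No surgery; 40% reduction at month 3, 100% at month 6 | No | Yes at month 3, no at month 6 | Depends on the visit used |

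No statement elsewhere in the article closes rows 2 to 4. The rule for surgery between randomization and embolization (Primary Outcomes and Discussion) also speaks only of surgical rescue. Nothing says that thickness after an evacuation is not to be used. The concomitant-care section does not exclude such surgery.

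In the last row, if month 3 counted, the patient would be a primary failure and also a complete resolution at 6 months on the secondary outcome.

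**2. Reproduce the planned sample size**

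Inputs from Sample size {14}: control 10%, intervention 1%, power 85%, two-sided alpha 0.05, 10% drop-out; 1:1 allocation from Trial Design {8}.

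Pooled-variance formula, with d = 0.09 and mean rate 0.055:

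n0 = [1.960·√(2·0.055·0.945) + 1.036·√(0.10·0.90 + 0.01·0.99)]² / 0.09² = 113.7

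Continuity correction:

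n = (n0/4)·[1 + √(1 + 4/(n0·d))]² = 135.0 per arm, or 270 in total

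270/0.90 = 300, which matches. Without the correction the result is 114 per arm, 228 in total, and 254 after drop-out, which does not match.

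**3. Illustrate the size (assumed counts)**

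Expected control failures are 0.10 × 135 = 13.5. Suppose k of them are evacuations scored as successes; the documents give no value for k. The control rate becomes p = (13.5 − k)/135, and d = p − 0.01. Inverting the correction gives n0 = (135 − 1/d)²/135. With mean rate m = (p + 0.01)/2,

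power = Φ{[d·√n0 − 1.960·√(2m(1 − m))] / √(p(1 − p) + 0.0099)}

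For k = 0: n0 = (135 − 11.11)²/135 = 113.7, and (0.9596 − 0.6319)/0.3161 = 1.037, so power is 85.0%.

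| k | Control rate | n0 | z | Power, corrected | Power, uncorrected (n0 = 135) |
|---|---|---|---|---|---|
| 0 | 10.0% | 113.7 | 1.037 | 85.0% | 90.5% |
| 2 | 8.5% | 109.7 | 0.666 | 74.7% | 83.1% |
| 4 | 7.0% | 103.9 | 0.259 | 60.2% | 71.6% |

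The corrected column is the one consistent with the plan's own calculation.

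**The case against.** Several points on the other side have weight.

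**The scale sentence may explain the rescue sentence.** It follows a statement about symptom onset and can be read as putting the word symptoms into operation. A reader might infer an outright contradiction between the two; the text does not go that far. But one requires growth without a threshold and the other sets thresholds without growth, so a patient can satisfy one and not the other. The need to reconcile them stands.

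**The rescue sentence is loosely worded.** It says *intended as*, and *relief or symptoms* is probably a slip for *relief of symptoms*. Correcting the slip leaves the restriction to symptoms with growth, and so the gap.

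**Scoring off-definition surgery could be left to an analysis plan.** That would be fair if the article were silent. It is not: it states a definition that places such surgery outside the failure event.

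**The natural reading of the imaging component is the state at 6 months.** This largely stands. A reader might infer that the protocol does score slow but complete resolvers as failures. It never says that the 3-month CT decides, so this is an ambiguity and not a demonstrated mis-scoring. No loss of power is attached to it, because the documents give no share of slow resolvers.

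**A symptom-based definition limits the influence of preference-driven surgery.** This is a real advantage in an open-label trial, and counting every evacuation gives it up. The choice is a trade-off, which is why the narrow definition should be kept as a sensitivity analysis.

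**The direction of bias is not established.** A reader might infer that control failures would be hidden, because ten times as many failures are expected there. Rescored control failures would work against embolization and rescored intervention failures in its favour. The documents do not show which would dominate.

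**Conclusion.** The point holds for the surgical component. As worded, an evacuation of the study hematoma within 6 months for a reason other than symptoms with continuous growth is not a failure, and the operation can itself make the patient a success. This follows from the two component definitions and needs no assumption about frequency. That it may differ by arm follows from open-label surgical decisions; its direction and amount are unknown.

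The power figures illustrate sensitivity and do not forecast a loss. They rest on assumed counts of 2 and 4, all in the control arm, with 135 evaluable patients per arm and the plan's own event rates. They show only that, with about 13.5 control failures expected, a few rescored patients matter. The planned 300 reproduces and is not disputed here.

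The imaging visit is a secondary point: an ambiguity in the primary endpoint that should be settled.

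**What to change.** Change the scoring text only; patient management is untouched.

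1. In the primary analysis, count any evacuation of the study hematoma from randomization to 6 months as failure, whatever the recorded indication. State that thickness measured after an evacuation cannot turn it into a success.
2. Judge the 50% criterion on the 6-month CT and treat the 3-month CT as supportive.
3. Add one sensitivity analysis that uses the current narrow rescue definition.
4. Reconcile the rescue definition with the mRS/Markwalder sentence. Which clinical criterion is right is for the investigators and is not judged here.

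The cost is a few sentences of outcome wording and one extra analysis, with the recorded reason for each evacuation available to run it. The downside is that preference-driven evacuations count as failures in the main analysis; the sensitivity analysis shows how much depends on them. The change should be made before outcome data by arm are seen, and so before the interim analysis planned when 150 patients have completed 6 months.

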#### Secondary outcomes

The following secondary outcomes will be assessed:

Successful embolization rate of the target vessels based on DSA.Complete resolution of cSDH at 6 months follow-up;Recurrence rate of cSDH at 12 months follow-up;Procedure related complication during or 30 day after MMA embolization;Adverse event related to conservative management 30 day after randomization.

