#### Secondary objectives

Secondary objectives of this study include assessment of:

Endovascular procedure related complications;Neurological deficits;Recurrence rate associated with endovascular embolization of MMA;Resolution rate.

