**Assessments**						
Demographics data﻿	X					
Medical history	X					
Laboratory data	X			X	X	X
Non contrast CT	X			X	X	X
mRS/Markwalder scale	X			X	X	X
DSA imaging		X				
EVT-Complications		X	X			
Adverse events			X	X	X	X

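### The neurological-deficit objective has no secondary outcome, and the two listed 30-day harm outcomes count different events from different starting points, so they should not be contrasted between arms

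*Protocol article*

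**What the plan says.** Secondary objectives names four aims. The first is "Endovascular procedure related complications"; the other three run "Neurological deficits;Recurrence rate associated with endovascular embolization of MMA;Resolution rate".

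Secondary outcomes lists five items: angiographic success of embolization, complete resolution at 6 months, recurrence at 12 months, and two harm outcomes. The harm outcomes are "Procedure related complication during or 30 day after MMA embolization" and "Adverse event related to conservative management 30 day after randomization".

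For the primary outcome the article takes care over the starting point: "Time zero is defined as the date of randomization for both groups in order to ensure comparability and avoid immortal time bias". It also recognises an interval before treatment in the embolization arm, since "any surgical rescue occurring after randomization but before the scheduled embolization procedure will be considered a treatment failure".

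Table 1 has a row "mRS/Markwalder scale" ticked at screening, 3, 6 and 12 months, and an adverse-event row ticked at 1, 3, 6 and 12 months. Neither row is split by arm. Section {17a} has a blinded physician in each centre collect clinical outcome at 3, 6 and 12 months. Section {22} requires all AEs and SAEs over the study period to be documented, and section {20a} reports procedure-related complications and AEs/SAEs as absolute and relative frequencies.

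**The concern.** There are two gaps between what the trial sets out to learn and what it lists as outcomes.

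First, an objective without an outcome leaves scale, threshold, time point and comparison open until the data are in. The primary composite does not close this gap. A patient whose hematoma shrinks by more than half without surgery counts as a success even if a new deficit has appeared.

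Second, the only two harm items on the outcome list each belong to one arm. They sit side by side with the same 30-day length, and section {20a} gives chi-square or Fisher's exact test as the general comparison for categorical data. A reader or analyst could easily set one rate against the other, and the difference would mix a treatment effect with differences in definition. The Discussion says the trial is needed to weigh benefit against risk, and the risk side of that needs a count made the same way in both arms.

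**Working it through.** **The plan's own figure.** The one computed design figure is the total of 300. Inputs from Sample size {14}: 10% versus 1%, 85% power, two-sided alpha 0.05, 10% drop-out.

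- Without continuity correction: n = [1.960·√(2·0.055·0.945) + 1.036·√(0.10·0.90 + 0.01·0.99)]² / 0.09² = 113.7, so 114 per arm.
- With continuity correction: n′ = (113.7/4)·[1 + √(1 + 4/(113.7·0.09))]² = 135 per arm, or 270 in total.
- Drop-out: 270 / (1 − 0.10) = 300.

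The figure reproduces. It rests on the primary outcome alone, so nothing below changes it.

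**Objectives set against outcomes.**

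| Secondary objective | Matching secondary outcome |
|---|---|
| Procedure complications | Yes: complications during the procedure or in the 30 days after |
| Neurological deficits | None |
| Recurrence | Yes: at 12 months |
| Resolution | Yes: complete, at 6 months |

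One of four has no outcome. The mRS and Markwalder scales appear under Primary Outcomes only to judge symptom onset and candidacy for evacuation. Section {18a} collects them as measures of disability, but section {20a} names no analysis for them.

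**The two harm outcomes side by side.**

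| Feature | Embolization arm | Control arm |
|---|---|---|
| Event | Complication | Adverse event |
| Attributed to | The procedure | Conservative management |
| Counting starts | At the procedure | At randomization |
| Counting ends | 30 days after the procedure | 30 days after randomization |

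Three consequences follow.

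1. *Clock.* If embolization takes place d days after randomization, the embolization-arm window runs from day d to day d + 30 and the control window from day 0 to day 30. They overlap for 30 − d days (for d up to 30), and the first d days in the embolization arm are not covered. The article does not give d. Table 1 puts randomization and embolization both at t0, so d may be small, but the rule for rescue before embolization shows that it is not zero by design.
2. *Population.* A patient allocated to embolization who never receives it has no window at all under the listed outcome, although the analysis principle is intention to treat.
3. *Attribution.* Calling an event related to the procedure or to conservative management requires knowing which was given. Treatment is open label, and the blinded clinical assessments in {17a} begin at 3 months, after both 30-day windows would usually have closed.

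**What is already collected.** Adverse events at 1 and 6 months, and mRS and Markwalder at 6 months, are scheduled in both arms. The scales are not scheduled at 1 month, so a 30-day neurological outcome would have to rest on adverse-event reports. The 6-month visit is the first scheduled scale assessment that coincides with the primary time point.

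**The case against.** The strongest reply is that safety and disability are both already covered. All AEs and SAEs are to be documented whatever the arm or cause, they are scheduled without a split by arm, and they are to be summarised as frequencies separately from procedure-related complications. The mRS and Markwalder scales are recorded in both arms, with blinded clinical assessment. The complication objective concerns the procedure, so a single-arm outcome answers it. Surgical rescue before embolization counts as a primary-outcome failure, and the primary composite has a clinical component. Regression models and effect measures can be left to an analysis plan.

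Most of this stands, and it limits the point. A reader might infer that neither disability nor safety can be compared between the arms; the documents do not support that, because the data for both comparisons are planned. A reader might also count the complication objective as lacking a valid comparison, but it promises none. Nor is the control-arm harm category shown to be nearly empty: control patients receive best medical treatment, and routine concomitant care is permitted in both groups, so attributable events can occur, and the article gives no rate.

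The reply does not reach two things. The article itself states both the list of objectives and the list of outcomes, and they do not match on neurological deficits; this is not detail left to another document. And a general summary of adverse events does not make the two listed harm outcomes comparable with each other.

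**Conclusion.** The point holds in this form: one of the four secondary objectives has no defined outcome, and the two listed 30-day harm outcomes differ in event type, attribution and time origin and should not be contrasted directly. The second part also departs from the common starting point that the article adopts for its primary outcome. A valid comparison of safety and disability remains feasible from planned data; what is missing is its designation as an outcome.

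The practical effect of the clock difference cannot be sized, because the delay from randomization to embolization is not given. If that delay is zero, the clock difference disappears, but the differences in event type and attribution remain, as does the gap for patients never embolized. The primary analysis and the sample size are untouched. The lists should be corrected, but the design does not depend on it.

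**What to change.** - Make the between-arm harm outcome any AE/SAE of any cause, counted from randomization in both arms by intention to treat, for example at 30 days and at 6 months, reported as a risk difference with 95% confidence interval. Procedural complications count within it.
- Keep procedure-related complications, during the procedure and in the 30 days after, as a descriptive table for the embolization arm, not set against a control-arm rate.
- Name mRS and/or Markwalder grade at 6 months, assessed by the blinded physician and compared between arms, as the secondary outcome for neurological deficits. The model can be left to the analysis plan.

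The cost is wording in the outcome list and statistical section, plus a little more analysis. The 1-month and 6-month adverse-event records and the 6-month scales are already scheduled, so no visits are added and the total of 300 stays as it is.

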#### Participant timeline {13}

All trial procedures including radiological and clinical visits are summarized in Table 1.

**Table 1 Tab1:** Schedule of enrollment, interventions and assessments

**Timing of all procedures in EMBOTRIAL-1**						
**Timepoint**	-t_1_	t_0_	1 month	3 months	6 months	1 year
**Enrollment**						
Eligibility screen	X					
Informed consent	X					
Randomization		X				
**Interventions**						
MMA embolization		X				
Conservative treatment		X				
**Assessments**						
Demographics data﻿	X					
Medical history	X					
Laboratory data	X			X	X	X
Non contrast CT	X			X	X	X
mRS/Markwalder scale	X			X	X	X
DSA imaging		X				
EVT-Complications		X	X			
Adverse events			X	X	X	X

#### Sample size {14}

Our estimates are based on treatment failure rates of previous published studies. Ban et al. [18] compared a prospective series of 72 patients with cSDH submitted to MMA embolization with a group control of 469 subjects undergoing standard treatment. In particular, in the amount of patients into embolization group, 27 (37.5%) were asymptomatic and underwent MMA embolization alone. No treatment failure was found during follow-up after embolization. Of 469 patients in the control group, 67 patients underwent close follow-up. Spontaneous resolution occurred in 11 (16.4%), but treatment failure with surgical rescue was needed in 56 (83.6%) for symptom development resulting from progression of hematoma. Moreover, Catapano et al. [21] reported a treatment failure rate of 17% and of 3%, respectively with conservative approach and MMA embolization. Other studies reported progression rate of conventional treatment ranged from 11 to 27.5% [22–24]. So we assume the event rate of the intervention group is 1%. The trial is powered to assess superiority. When assuming the event rate of 1% in intervention group and 10% event rate in the control group, with a power of 85% and two-sided alpha of 0.05, allowing for 10% drop-outs, the estimated sample size is 300 patients in total.

#### Recruitment {15}

During the kick-of meeting, the clinical investigators of each center will be trained in communicating with potential participants and their relatives, documentation including screening logs, and other standard operating procedures. All the centers will recruit patients competitively, and recruitment progress will be reported to the steering committee at 6, 9, 15, 21 months after randomization of the first patient, to track the recruitment process. The estimated rate of recruitment is 3 to 5 patients per month in high volume centers and 1–2 patients in medium-low volume centers, and the expected recruitment time will last 2 years. In case of insufficient enrollment (i.e., <25% of the number of patients included at the fixed time points), investigators will take extra measures to increase recruitment (e.g., increasing awareness among trial supporting personnel, include other institutions, etc.).

